## Abstract

**Background:**

The increasing role of consumer electronics and Web-enabled mobile devices in the medical sector opens up promising possibilities for integrating novel technical solutions into therapy and patient support for oncologic illnesses. A recent survey carried out at Heidelberg University Hospital suggested a high acceptance among patients for an additional approach to patient care during radiotherapy based on patient-reported outcomes by a dedicated mobile app.

**Objective:**

The aim of this trial (OPTIMISE-1: Oncologic Therapy Support Via Means of a Dedicated Mobile App – A Prospective Feasibility Evaluation) is to prospectively evaluate the feasibility of employing a mobile app for the systematic support of radiooncological patients throughout the course of their radiotherapy by monitoring symptoms and patient performance, and facilitating the background-exchange of relevant information between patient and physician.

**Methods:**

The present single-center, prospective, exploratory trial, conducted at Heidelberg University Hospital, assesses the feasibility of integrating an app-based approach into patient-care during radiotherapy. Patients undergoing curative radiotherapy for thoracic or pelvic tumors will be surveyed regarding general performance, treatment-related quality of life (QoL) and symptoms, and their need to personally consult a physician by means of a mobile app during treatment. The primary endpoint of feasibility will be reached when 80% of the patients have successfully answered 80% of their respective questions scheduled for each treatment day. Furthermore, treatment-related patient satisfaction and health-related QoL is assessed by the Patient Satisfaction Questionnaire Short Form (PSQ-18) and the European Organization for Research and Treatment of Cancer (EORTC) questionnaires at the beginning (baseline) and end of radiotherapy, and at the first follow-up.

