### Assessment of Primary and Secondary Endpoints

The primary aim of this study is to assess the feasibility of an app-based therapy support. It will be assessed by the primary endpoint—the proportion of patients who answered at least 80% of the app-based questions during their radiotherapy as outpatients. For every study subject, the number of answered questions is documented on each day of radiotherapy for the assessment of the primary endpoint. This definition of feasibility was derived mainly from clinical and logistical considerations. Due to logistical difficulties unrelated to the trial (eg, personnel change, transfer of patients to different radiation units due to technical maintenance), a certain portion of treatment days is to be expected where some patients fail to receive the survey tablet device. Since there is no previous systematic data on this specific issue, we estimate the portion of those expected irregularities at a realistic 20% based on clinical experience.

The following secondary endpoints are considered:

Patient satisfactionNumber of medical consultationsDuration of medical consultations (in min)Need for toxicity-caused hospitalizationHealth-related QoL

Patient satisfaction is measured by the PSQ-18, which includes 18 items in 7 subscales: general satisfaction, technical quality, interpersonal manner, communication, early reaction to treatment side effects, time spent with doctor, accessibility and convenience. Responses to each item are given on a 5-point scale, and based on the questionnaire, a total sum score will be calculated and transformed to a scale ranging from 1 to 5.

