### Statistical Analysis

The calculation of the sample size was done with respect to the primary endpoint and the primary analysis. Using the exact binomial test, we aim to show that the primary endpoint is reached at values of ≥80% of all study subjects answering ≥80% of the app-based questions during their radiotherapy as outpatients. With a sample size of 50 patients in this pilot study and an assumed percentage of 92% for the primary endpoint, a power of 1-β=80% is reached with a one-sided significance level of α=5%. Considerations regarding sample size and power were done using the *PROC POWER* procedure in SAS (version 9.4). The primary endpoint will be evaluated using the exact binomial test, which is the primary analysis. The one-sided significance level for this feasibility study is set to 5%.

Methods of descriptive data analysis will be used to describe patient characteristics and secondary outcomes, including calculation of appropriate summary measures of the empirical distribution, such as mean and standard deviation, median and interquartile range for continous variables, as well as absolute and relative numbers for categorical variables. Additionally, according to tumor type, subgroup analyses will be performed as a sensitivity analysis. Additionally, multivariable regression models will be used to analyze the relationship between patient characteristics and the primary endpoint. However, we will consider the primary variable on the original scale without any cut-off value (ie, the relative number of app-based answered questions) as the outcome variable and, thus, linear regression models will be applied. Age, gender and the need of toxicity-caused hospitalization will be included as predictors. The same model will be applied for the secondary endpoints. In addition, correlations will be considered. Graphical methods will be applied to visualize the results.

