### Limitations and Future Perspectives

In the current study, the survey app is not deployed using the patient’s own mobile device but is installed on a tablet computer belonging to the investigator and integrated into the institution’s information technology infrastructure according to data protection regulations. For future trials, it is planned (after establishing feasibility and usefulness) to expand the scope of the app so that patients can use their own devices for survey completion outside the clinic.

On the other side, the aforementioned approach may contribute to addressing a possible selection bias. By presenting the application to patients on an institution-owned tablet device, we do not exclude patients who do not themselves own a mobile device, thus testing the application on patients regardless of their technical abilities and/or affinity.

The definition of feasibility in this trial is largely derived from intrainstitutional clinical experience and logistical considerations. There is, however, to date no systematic data from which a more general definition of feasibility can be derived in this context. A systematic survey conducted at our institution on oncologic patients’ use of and affinity towards mobile devices is in accordance with previously published data [13] in suggesting that roughly three quarters of patients would be inclined to use a mobile app in the context of radiotherapy. This further suggests that expecting a patient compliance of 80% to demonstrate feasibility is realistic.

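### The 80% wording of the success criterion does not match the primary test: 40 to 44 of 50 patients would count as feasible under the wording but not under the test

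*Protocol article*

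**What the plan says.** Four places in the protocol article bear on when feasibility is concluded.

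- **Abstract, Methods:** "feasibility will be reached when 80% of the patients have successfully answered 80% of their respective questions scheduled for each treatment day". This puts a threshold on the observed share of patients and mentions no test.
- **Assessment of Primary and Secondary Endpoints:** the endpoint is "the proportion of patients who answered at least 80% of the app-based questions during their radiotherapy as outpatients". This fixes the patient-level criterion over the whole outpatient course. It sets no success threshold for the group.
- **Statistical Analysis:** "we aim to show that the primary endpoint is reached at values of ≥80% of all study subjects answering ≥80% of the app-based questions", and then "The primary endpoint will be evaluated using the exact binomial test, which is the primary analysis". The planning figures are "With a sample size of 50 patients in this pilot study and an assumed percentage of 92% for the primary endpoint" and "a power of 1-β=80% is reached with a one-sided significance level of α=5" per cent. The same one-sided level is set for the analysis. No null hypothesis is written down.
- **Discussion, Limitations and Future Perspectives:** "expecting a patient compliance of 80% to demonstrate feasibility is realistic".

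**The concern.** An observed proportion of 80% and a test that rejects a true proportion of 80% are different hurdles. The Abstract places 80% on the success side, and so does the at-least-80% phrase in Statistical Analysis. A one-sided test against 80% places that value in the null, and with 50 patients it can reject only when the observed share is well above 80%.

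The trial has one primary conclusion, feasible or not, and the Conclusions section presents it as groundwork for larger evaluations. If the result falls between the two hurdles, an author could cite one sentence to claim feasibility and a reader could cite another to deny it. The choice would then be made after the data are known.

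**Working it through.** **Inputs.** N = 50, assumed rate p1 = 0.92, one-sided α = 0.05, exact binomial test and stated power 80% all come from Statistical Analysis. The reference value p0 = 0.80 is inferred, because it is the only reference proportion the article gives for the share of patients.

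**Formula.** For X successes among 50 patients, P(X ≥ r | p) = Σ C(50,k) p^k (1−p)^(50−k), summed over k = r to 50.

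**Step 1: reproduce the stated power.** The critical value is the smallest r with P(X ≥ r | 0.80) ≤ 0.05.

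| r | Size at 0.80 | Power at 0.92 |
|---|---|---|
| 44 | 0.103 | 0.898 |
| 45 | 0.048 | 0.792 |
| 46 | 0.018 | 0.629 |

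The critical value is 45, that is 45/50 = 90%. The power of 0.792 agrees with the stated 80% to within one percentage point. Other readings fit less well: the normal approximation gives 0.759 one-sided and 0.594 two-sided. So the sample size statement belongs to a one-sided exact test with 80% as the value to be exceeded.

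**Step 2: the literal rule.** 0.80 × 50 = 40, so 40 of 50 is enough.

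**Step 3: where the two disagree.** The one-sided exact p-value against 0.80 is P(X ≥ x | 0.80). The lower limit is the one-sided 95% Clopper–Pearson limit.

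| Observed | Share | p-value | Lower limit | Literal 80% | Test |
|---|---|---|---|---|---|
| 40 | 80% | 0.584 | 0.684 | feasible | not shown |
| 41 | 82% | 0.444 | 0.707 | feasible | not shown |
| 42 | 84% | 0.307 | 0.730 | feasible | not shown |
| 43 | 86% | 0.190 | 0.753 | feasible | not shown |
| 44 | 88% | 0.103 | 0.777 | feasible | not shown |
| 45 | 90% | 0.048 | 0.801 | feasible | feasible |

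**Step 4: how often it matters.** The last column is the difference of the two before it.

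| True rate | P(X ≥ 40) | P(X ≥ 45) | P(40 to 44) |
|---|---|---|---|
| 0.75 | 0.262 | 0.007 | 0.255 |
| 0.80 | 0.584 | 0.048 | 0.536 |
| 0.85 | 0.880 | 0.219 | 0.661 |
| 0.90 | 0.991 | 0.616 | 0.375 |
| 0.92 | 0.998 | 0.792 | 0.206 |

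**Step 5: sensitivity.**

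- *Null value.* The lower limits for 44 and 45 successes are 0.777 and 0.801. Any null value between them gives the same cut-off of 45, so the result does not hinge on 80% to the last decimal.
- *Denominator.* With 45 patients analysed, the literal rule needs 0.80 × 45 = 36 and the exact test needs 41. The counts move, but the gap stays.

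**The case against.** The best reply is that Statistical Analysis already settles which analysis governs. It names the exact test as primary, sets its level and powers the trial on it. An assumed rate of 92% would make little sense if observing 80% were enough. On this view the Abstract gives the benchmark and the Methods say how it is tested. Most of this stands: a careful analyst would run the test, and no section states 40 of 50 as a cut-off. It does not remove the problem, because Statistical Analysis itself describes the endpoint as reached from 80% upwards and states no null hypothesis. The looseness is therefore not just abstract shorthand.

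A journal article may also leave the critical count to an analysis plan. That is fair, and the missing count is not the complaint. The complaint is a stated threshold that conflicts with the stated test.

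A reader might draw three stronger conclusions that the article does not support:

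- *That the plan has no governing rule or no type I error control.* It names a primary analysis at a one-sided 5% level, and that test has size 0.048.
- *That the Discussion sets a rival rule, which the test nearly always fails.* The sentence concerns what is realistic to expect. It does not say whether 80% means the share of questions or the share of patients. If it is the null value for patients, a 4.8% pass rate there is the test working as intended.
- *That the Abstract requires 80% on every single day.* The reference to each treatment day most naturally describes how questions are scheduled, and the endpoint section defines the criterion over the whole course.

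**Conclusion.** The point holds as a contradiction between the stated success threshold and the designated primary analysis. With 50 patients analysed and 80% as the null value, the literal wording passes at 40 and the test at 45, so five possible results (40 to 44) lead to opposite conclusions. That range has a probability of 21% even if the planning assumption of 92% is true, and of 54% to 66% for true rates of 80% to 85%. At 40 of 50 the data would still be compatible with a true rate as low as 68%.

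The conclusion rests on two assumptions: that 80% is the null value, which is inferred from the text and supported by the reproduced power, and that all 50 patients are analysed. The sample size, the test and the endpoint definition do not need to change. The defect is one of wording, but it bears directly on the trial's only primary conclusion and should be settled before the data are analysed.

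**What to change.** 1. In Statistical Analysis, state H0: p ≤ 0.80 against H1: p > 0.80, where p is the true proportion of patients meeting the course-wide criterion in Assessment of Primary and Secondary Endpoints. Replace the phrase that has the endpoint reached at 80% or more.
2. State that feasibility is concluded only if the one-sided exact p-value is at most 0.05, which is the same as a one-sided 95% exact lower limit above 80%. Add that this means at least 45 of 50 if all 50 are analysed, and that the count is recomputed for any other denominator. A bare count of 45 should not stand as the rule.
3. Reword the Abstract to match, using the course-wide endpoint definition.
4. In Limitations and Future Perspectives, say that 80% is the benchmark to be exceeded.

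No new data, patients or analyses are needed. The small downside is that the success bar becomes visibly about 90% observed. Readers will also see that the chance of meeting it is 62% at a true rate of 90% and 22% at 85%. Those chances already apply under the planned test.

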**Results:**

This trial will recruit 50 patients over a period of 12 months. Follow-up will be completed after 18 months, and publication of results is planned at 24 months after trial initiation.

**Conclusions:**

This study will serve as a basis for future studies aiming to exploit the constant innovation in mobile medical appliances and integrate novel patient-centered concepts into patient care in the context of radiotherapy.

**Trial Registration:**

ClinicalTrials.gov NCT03168048; https://clinicaltrials.gov/ct2/show/NCT03168048 (Archived at WebCite http://www.webcitation.org/6wtWGgi0X)

## Introduction

The role of consumer electronics and Web-enabled mobile devices in the medical sector is ever increasing, broadening the scope for mobile health apps [1]. The availability and market share of such appliances, summarized by the World Health Organization under the term “mobile health” (mHealth), has steadily grown over the past years [2]. Areas of use include assistance in appointment-making, the monitoring of certain parameters in patients with chronic illnesses or the regular documentation of pain or other symptoms [3-5]. Initial experience for the use of mobile apps in the area of oncology has shown promising results: A prospective pilot trial was able to demonstrate significantly improved overall survival for lung cancer patients, who were systematically telemonitored with the help of a mobile phone app based on patient-reported data and using the dynamics of patients’ clinical symptoms for risk-stratification and individualized follow-up [6]. This study showed that the use of an app-based identification of high-risk patients may help to initiate earlier treatment, contributing to improved patient outcomes. Furthermore, the patient compliance within the scope of a systematic follow-up regimen proved superior to the control group whose follow-up only consisted of regular computed tomography scans and no additional supervision by a mobile phone–based app [7].

On the other hand, a survey among German health care providers showed a high readiness to incorporate the use of mobile health apps into oncologic treatment regimens, thereby utilizing the obvious advantages of mobile devices in patient care [8]. In this survey, the ability to monitor patient performance more closely even over longer geographical distances, the possibility to overcome language barriers or selectively address special needs of patient subgroups, such as ethnic minorities or children, were reported among the main advantages of mHealth in the field of oncology [9,10].

At present, the spectrum of apps available in the oncologic field is still rather limited and lacks validation by larger systematic analyses, so that the relevance of mobile apps for patient care and therapy support during prolonged oncologic treatments, such as radiotherapy or chemotherapy, remains largely unclear [11].

Based on the promising preliminary results of a systematic survey being conducted at Heidelberg University Hospital among a large number of cancer patients demonstrating a high acceptance of mobile app–based measures of therapy support, the present OPTIMISE-1 trial (which stands for **O**ncologic Thera**p**y Suppor**t** V**i**a **M**eans of a Ded**i**cated Mobile App – A Pro**s**pective F**e**asibility Evaluation) aims to assess the feasibility of introducing a mobile app to the treatment schedule of patients undergoing radiotherapy, as well as measuring its impact on patient satisfaction and health-related quality of life (QoL).

## Methods

### Study Design

The present study is designed as a prospective, single-center pilot study and will be conducted at Heidelberg University Hospital’s Department of Radiation Oncology. Cancer patients undergoing radiotherapy are offered a novel model of therapy support during the course of treatment, where a mobile app will be used to monitor patient-reported outcomes concerning general performance and therapy-related symptoms, and enable patients to express the need to see a physician when clinical symptoms occur. The length and frequency of consultations with a physician will be analyzed to assess the economic aspect of the model. Furthermore, the necessity of admitting a patient to inpatient care during the course of therapy will be documented together with the timepoint of admission. Since routine bloodwork is independently conducted at regular intervals for all patients undergoing radiotherapy, the data from this bloodwork together with the clinical parameters documented in this study (eg, symptoms, toxicity, etc) will be screened for predictive factors for the necessity of inpatient admission by means of correlation. This is done as part of an exploratory side analysis unrelated to the primary objective of this study.

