Health-related QoL is assessed by the EORTC QLQ-C30 questionnaire in addition to the diagnosis-specific questionnaire module (eg, BR23 for breast cancer or PR25 for prostate cancer). Patients are prompted to fill out these questionnaires prior to the initiation of radiotherapy, at the time of treatment completion and at the first follow-up visit, which is routinely scheduled at 6-8 weeks after the completion of therapy. The duration and number of all visits during radiotherapy is documented to estimate the average cost of this form of therapy support. Per our SOP, the beginning and end of every consultation for all patients is documented by the physician by setting status flags within the Radiation Oncology Clinic Information System (ROKIS). The duration of every consultation can then be extracted by querying the ROKIS database. The software solutions in use for those purposes at our institution are MOSAIQ (ELEKTA, Stockholm, Sweden) for ROKIS and Crystal Reports (SAP, Walldorf, Germany) for generating database reports.

Table 1 shows the intervention and assessment schedule for the trial. The Standard Protocol Items: Recommendations for Interventional Trials (SPIRIT) checklist [12] on different protocol items related to this trial is included in Multimedia Appendix 1.

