## Discussion

### Study Rationale

As consumer electronics become increasingly employed in the medical sector, their use for the support of oncologic patients opens up a range of possibilities from the gathering of information on patient health and symptoms to patient notification about appointments or test results. The present single-center prospective pilot trial conducted at the Department of Radiation Oncology of Heidelberg University Hospital explores the possibility of employing a mobile app for the systematic support of radiooncological patients throughout the course of their radiotherapy by monitoring symptoms and patient performance, and facilitating the exchange of relevant information between patient and physician. We aim to assess the feasibility and patient acceptance of incorporating such a mobile app into active patient care. Furthermore, we aim to estimate the economic and financial aspects of this novel approach to therapy support.

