### Conclusions

The findings of this study will play an important role in clinically validating the mobile app we have developed for the collection of patient-reported outcome measures from patients undergoing radiotherapy. By proving the usefulness and feasibility of an app-based approach to radio-oncologic patient supportive care, the present exploratory study prepares the ground for the larger-scale evaluations we are planning to perform on this promising subject.

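### With one arm and no reference group, the trial can describe quality of life, satisfaction and cost under app support, but cannot measure the app's impact or prove its usefulness

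*Protocol article*

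**What the plan says.** **Design.** The protocol article (Study Design) states: "The present study is designed as a prospective, single-center pilot study". All participants are offered app support. App-Based Therapy Support describes usual care outside the trial as weekly physician visits plus bloodwork, and presents trial care as additional to it. Usual care is not used as a reference anywhere.

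**Aims and conclusions.**
- Introduction: besides feasibility, the trial aims at "as well as measuring its impact on patient satisfaction and health-related quality of life (QoL".
- Limitations and Future Perspectives: the move to patients' own devices is to follow once feasibility and usefulness have been established.
- Conclusions: "By proving the usefulness and feasibility of an app-based approach to radio-oncologic patient supportive care", the study prepares larger evaluations.
- Study Design: "The length and frequency of consultations with a physician will be analyzed to assess the economic aspect of the model".
- Study Rationale: "we aim to estimate the economic and financial aspects of this novel approach to therapy support".

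**How the economic aim is made concrete.** In Assessment of Primary and Secondary Endpoints, the number and duration of visits are recorded "to estimate the average cost of this form of therapy support". The same section says that "the beginning and end of every consultation for all patients is documented by the physician by setting status flags" in the clinic information system (ROKIS), from which durations can be queried.

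**Analysis.** Statistical Analysis sizes and tests only the feasibility proportion. Secondary outcomes are described, regressed on age, gender and toxicity-caused hospitalization, and examined by correlation.

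**The concern.** Impact and usefulness are comparative ideas: they ask how patients fare with the app against how they would have fared without it. A design in which everyone has the app contains no information on the second half of that question. If the published report follows the stated aims, a change in quality of life over radiotherapy, or a high satisfaction score at its end, could be presented as an effect of the app. The Limitations section makes the next step of the programme depend on usefulness as well as feasibility, so the word carries weight. That section does not mention the missing comparator.

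The economic aim carries a milder form of the same risk. Because trial care is usual care plus visits requested through the app, a reader will naturally ask whether the app adds or saves physician time, and a mean from trial patients alone does not answer that.

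**Working it through.** **1. What the trial is sized for.** Inputs from Statistical Analysis: n = 50, null 80%, assumed 92%, one-sided α = 5%, exact binomial test. The smallest rejection count with P(X ≥ r | 50, 0.80) ≤ 0.05 is r = 45.
- Exact α = P(X ≥ 45 | 50, 0.80) = 0.0480
- Power = P(X ≥ 45 | 50, 0.92) = 0.7919

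This reproduces the stated 80% closely. It supports a statement on feasibility and nothing else.

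**2. What one arm says about quality of life.** The EORTC questionnaires are completed before radiotherapy, at its end and at the first follow-up, 6-8 weeks later. Write the mean change in trial patients as

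Δ = R + A,

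where R is the change over the treatment course without the app (toxicity and recovery) and A is the change due to the app. To obtain A one needs R, that is, the change in comparable patients without the app. The plan has no such patients, so A is not identified and a larger n would not help. The planned regressions do not help either, because having the app does not vary between participants. The share of questions answered does vary, but the plan treats it as an outcome, and by its own account it partly reflects whether the tablet reached the patient.

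**3. Satisfaction.** The Abstract gives the PSQ-18 at baseline, end of radiotherapy and first follow-up. Table 1 marks it at end of radiotherapy only. On the Table 1 schedule there is not even a within-patient change to describe.

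**4. What one arm can say about cost.** A mean over 50 patients (visits, minutes or cost per patient) has a 95% interval of half-width

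t(0.975; 49) × SD / √50 = 0.28 SD.

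So average cost under app support can be estimated. The difference from usual care is (mean with app) − (mean without app), and the second term is not collected. The weekly visit schedule of usual care gives partial context for visit number. It does not give the number of unscheduled visits in usual care, or minutes.

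**5. What a ROKIS reference could add.** ROKIS is described only as holding consultation start and end times. Recruitment gives roughly 1000 patients available for screening yearly and an assumed consent ratio of 5%-10%, that is 1000 × 0.05 = 50 to 1000 × 0.10 = 100 participants. The number of non-participants who meet all eligibility criteria is not stated, so control numbers are assumptions shown as a range. The detectable difference against 50 app patients (80% power, two-sided 5%, both assumed) is (1.960 + 0.842) × √(1/50 + 1/m) in SD units:

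| Controls m | Detectable difference |
|---|---|
| 50 | 0.56 SD |
| 100 | 0.49 SD |
| 200 | 0.44 SD |
| 950 (1000 − 50, upper bound) | 0.41 SD |

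No SD is given, so these cannot be turned into minutes. They ignore confounding and are therefore a best case.

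**The case against.** The strongest defence is that the plan's analysis is already modest. The trial is called a pilot and exploratory, secondary outcomes are handled descriptively, no test of an app effect is planned, and larger evaluations are left to later studies. One arm is adequate for the primary feasibility aim. All of this stands. It narrows the fault to the stated aims and conclusions, but does not remove it: the Introduction lists impact as an aim, and usefulness appears in two places as something the trial will have shown.

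A reader might go further and infer that the economic aim cannot be answered as designed. The documents do not support that. The endpoint section defines the quantity as the average cost of this form of support, which one arm can describe, and no passage promises a saving or a comparison with usual care.

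A reader might also infer that several hundred comparable patients are available free of cost. Recruitment speaks only of patients available for screening. Target Population excludes most patients with cervical, esophageal, anal and rectal cancers. The consent described is that of trial participants, and the documents do not address research use of other patients' records.

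Finally, a ROKIS comparison is fragile. With assumed consent of 5%-10%, participants are a selected group. This also stands, and is why such a comparison can only be exploratory.

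**Conclusion.** The point holds for impact and usefulness. No result this trial can produce would support either claim, because the app effect is not separable from the course of radiotherapy and there is no reference group. This rests only on the design as described and needs no numerical assumption. It is not a detail that an analysis plan could supply, since an analysis plan cannot create a comparator that the design lacks.

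For the economic aim the point is limited. Average cost under app support is estimable, to about ±0.28 SD for a per-patient mean with 50 complete records. Only a statement on physician time added or saved would be unsupported. A ROKIS reference could give that statement some basis, with detectable differences of roughly 0.41 to 0.56 SD before any allowance for confounding. It would do nothing for quality of life or satisfaction, because the documents do not say that ROKIS holds questionnaire data on non-participants.

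The primary endpoint and its test are not affected. The correction should be made because it changes what the trial may conclude.

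**What to change.** 1. **Reword the aims and conclusions.** In the Introduction, replace the aim of measuring impact with describing quality of life and satisfaction under app support. In Limitations and Future Perspectives and in Conclusions, drop usefulness as something established or proved, and keep feasibility. Name the missing comparator as a limitation.
2. **Limit the economic aim.** In Study Design and Study Rationale, state it as the average cost of app-supported care, as the endpoint section already does, with no statement on physician time added or saved.
3. **Optional, only if an incremental statement is wanted.** Prespecify an exploratory, non-randomised ROKIS comparison of consultations per week and minutes per week with concurrent outpatients who meet the same eligibility criteria, matched or adjusted for diagnosis, age and gender. State how many such patients there are, and state the confounding by consent.

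Items 1 and 2 cost a few sentences and leave trial conduct and the primary analysis as they are. Item 3 costs an extended database query, the matching or adjustment, and a check of the ethics position on using non-participants' records. Its main downside is residual confounding.
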